**Fig 2 pone.0303837.g002:**
[figure not shown]
Difference in differences example (reproduced from Sanders and Murphy, forthcoming [67]).

#### Statistical methods for analysis of impact

Our analytical strategy for the survey data will follow a matched difference in differences approach. Matching will take place prior to analysis in order to select the most appropriate sample.

The difference in difference strategy for this data will be to take the first time period as baseline survey data for both the treatment and counterfactual groups, and to make use of the endline survey data as the second time period.

*Imputation strategy*. Inspection of the missing data pattern will provide some initial insight in the type of missingness, and statistical testing will further help assess whether the missing data mechanism is Missing Completely At Random (MCAR) or Missing At Random (MAR). We will utilise Little’s MCAR test [68], which determines whether the missingness is related to the observed and unobserved data. We will also use a logistic regression model with an indicator of missingness as the outcome, which will show whether relevant covariates are predictive of missingness, pointing towards the plausibility of a MAR assumption.

Due to the nature of survey data collection, we anticipate missing data for some participants. We will not make use of imputation for outcome measures as this carries substantial risks in terms of bias. For missing data at baseline we will make use of a mixture of Multiple Imputation through Chained Equations (MICE) [69], in which available baseline or demographic data for the participant are used in regression analyses to calculate the likely values of the missing variable. Following imputation of missing data, we will examine the convergence diagnostics to ensure that the imputation process is stable and the imputed values are plausible.

*Analytical specification*. *Primary analysis – surveys*. Our primary analysis specification will be conducted using ordinary least squares/linear prediction model regressions, specified as;

$$Y_{ilt}=\alpha +\;\beta_{1}Y_{ilt-1}+\beta_{2\;}B_{l}+\Gamma_{1}X_{i}+\Gamma_{2}L_{l}+\epsilon_{lt}$$

Where;

*Y*_*ilt*_ is the outcome measure for individual i in local authority l at endline.

*α* is a regression constant

*Y*_*ilt*−1_ is the lagged value of the participant’s outcome measure at baseline.

*B*_*l*_ is a binary indicator of whether the participant was eligible for the basic income payments, set to 1 if they are and 0 else (equivalent to a binary indicator for being in the eligible cohort

*X*_*i*_ is a vector of participant level characteristics.

*L*_*l*_ is a vector of local authority fixed effects

*ϵ*_*lt*_ is an error term clustered at the level of the local authority/time period level.

*Follow-up (t) only data*. Some variables in the survey are only collected at follow-up (time t), and not at baseline (time t-1). For these variables, we will adopt a less typical approach and replace *Y*_*ilt*−1_ with a vector of baseline variables that are the strongest control group predictors of the outcome at time t.

*Primary analysis - administrative data*. Our primary analysis specification will be conducted using ordinary least squares/linear prediction model regressions, specified as;

$$Y_{ilt}=\alpha +\;\beta_{1}T_{t}+\beta_{2\;}B_{l}+\beta_{3}(T_{t}\cdot B_{l})+\Gamma_{1}X_{i}+\Gamma_{2}Q_{l}+\epsilon_{lt}$$

Where;

*Y*_*ilt*_ is the outcome measure for individual i in local authority l in time t.

*α* is a regression constant

*T*_*t*_ is a binary indicator of whether or not the time period in question is that in which the intervention is active.

*B*_*l*_ is a binary indicator of whether the participant was in a local authority that would make them eligible for the basic income payments, set to 1 if they are and 0 else (equivalent to a binary indicator for being in Wales).

(*T*_*t*_∙*B*_*l*_) is an interaction term between treatment local authority and treatment time period, which takes values of 1 only for Welsh local authorities during the time period when the intervention is active. This is our treatment variable and its coefficient is our coefficient of interest.

X_i_ is a vector of participant level characteristics.

*Q*_*l*_ is a vector of local authority level characteristics including those used in matching.

*ϵ*_*lt*_ is an error term clustered at the level of the local authority/time period (the level at which the treatment status varies).

*Secondary Analysis*. Secondary analysis will follow the same regression specification as our primary analysis, but replacing the variable Y with the relevant secondary outcomes.

*Robustness Checks*. We will robustness check our analyses by:

Using Null imputation across the board, replacing MICEConducting complete case analysisUsing logistic and probit regression for binary outcomes

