*Difference in differences*. Difference in Differences approaches are quasi-experimental approaches which compare the differences between treated and counterfactual units, before and after the introduction of a new policy or intervention (Fig 1 below). This comparison allows for time invariant differences, whether observed or unobserved to be controlled for analytically [66]. We will undertake two different versions of the difference in difference approach for our two separate data sources. For administrative data, we will make use of a standard difference in difference in which participants in Wales are compared with matched English care leavers, covering the same time period (and same life stage) as the Welsh Data. For our survey outcomes, due to the challenges associated with collecting data from English care leavers, we will instead draw our counterfactual group from the subsequent cohort of Welsh care leavers. Although the comparison of two groups that have not been measured contemporaneously (as is the case comparing Welsh Care leavers in one cohort with Welsh Care leavers in another) is a non-standard implementation of the difference in differences methodology, the underlying assumptions remain the same. Instead of assuming common trends in the macroeconomic conditions (as would be the case for a standard DID), we are instead assuming common trends over the same period of the life course – that is, we assume that outcomes change in the same ways for young people between their 18^th^ and 20^th^ birthday, for young people whose 18^th^ birthdays were up to a year apart. The broad approach to a Difference in Differences approach can be seen in Fig 2.

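### The survey analysis is described as a difference in differences under common trends, but its primary equation is a lagged-outcome model that rests on a different assumption

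*Protocol article*

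**What the plan says.** In Outcomes and data sources, the paragraph on difference in differences credits the method with removing stable group differences: "This comparison allows for time invariant differences, whether observed or unobserved to be controlled for analytically". It then presents the survey analysis as a non-standard version of that method whose assumptions are unchanged, and names the identifying assumption: "we are instead assuming common trends over the same period of the life course".

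Statistical methods for analysis of impact repeats the label ("Our analytical strategy for the survey data will follow a matched difference in differences approach") and says the strategy is "to take the first time period as baseline survey data for both the treatment and counterfactual groups", with the endline survey as the second period.

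The primary survey equation in the same section has these parts:
- The dependent variable "is the outcome measure for individual i in local authority l at endline".
- A baseline term with its own coefficient β1, which "is the lagged value of the participant’s outcome measure at baseline".
- The treatment term B, which "is a binary indicator of whether the participant was eligible for the basic income payments, set to 1 if they are and 0 else".
- Participant characteristics X and local authority fixed effects L.

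It has no period term, no period-by-cohort interaction, no change score and no individual effect. The administrative-data equation does contain a period-by-group interaction, of which the article says: "This is our treatment variable and its coefficient is our coefficient of interest".

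**The concern.** The two models identify the effect in different ways. A difference in differences subtracts the whole baseline gap and needs the cohorts to share a trend. A lagged-outcome model subtracts only β1 times the gap and needs cohort membership to be unconfounded once the baseline outcome, X and local authority are held fixed. The estimates differ whenever the cohorts differ at baseline and β1 is not 1.

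The cohorts are not randomised. They are a year apart, and the Discussion expects them to face different labour-market and cost-of-living conditions. The intervention baseline survey closed at 64% response after its collection process was changed part-way. Equal expected baselines therefore cannot be taken for granted.

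Six of the seven outcome domains in Table 1 draw on survey data. As written, the report could claim control of unobserved time-invariant differences for estimates that do not have it.

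**Working it through.** **The plan's own figure.** The Sample size paragraph gives a detectable survey effect of 0.2 SD, attributed to experience, so there is no formula to reproduce. As a plausibility check, assume two equal arms of 635 × 0.64 ≈ 406, two-sided 5% and 80% power; the article states neither alpha nor power and gives no comparator size. The unadjusted detectable effect is (1.960 + 0.842) × √(2/406) = 0.197 SD. The stated 0.2 SD is compatible with that. It serves below only as a yardstick.

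**Algebra.** Let τ be the true effect and d the baseline gap between cohorts left after matching, X and local authority.
1. Under common trends the endline gap is τ + d.
2. The survey equation removes β1·d, so the coefficient on B is τ + d − β1·d = τ + (1 − β1)d.
3. A difference in differences fixes β1 at 1 and returns τ.
4. With equal variances at the two waves, β1 is about the baseline-endline correlation ρ.

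**Size.** Neither d nor ρ is in the document; both are assumed. Bias in SD units, (1 − ρ)d:

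| d | ρ = 0.4 | ρ = 0.5 | ρ = 0.6 |
|---|---|---|---|
| 0 | 0 | 0 | 0 |
| 0.1 | 0.06 | 0.05 | 0.04 |
| 0.2 | 0.12 | 0.10 | 0.08 |

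**Simulation.** Settings: 406 per arm, 22 local authority effects, a persistent cohort difference, true effect zero, 1,000 runs per setting, ordinary standard errors and no matching step (so d is the gap that remains). At d = 0.2 and ρ = 0.5 the lagged-outcome model averaged 0.098 SD, with a false-positive rate of 36%. At d = 0 its rejection rate was 4 to 6%. The change score stayed within 0.005 SD of zero in every setting, with rejection of 3.7 to 6.8%.

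**Precision.** The variance of the lagged-outcome estimate is proportional to 1 − ρ², and that of the change score to 2(1 − ρ). The ratio is 2/(1 + ρ), which exceeds 1 for every ρ below 1. Detectable effects at 406 per arm, same assumptions:

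| ρ | Variance ratio | Lagged outcome | Change score |
|---|---|---|---|
| 0.3 | 1.54 | 0.188 | 0.233 |
| 0.5 | 1.33 | 0.170 | 0.197 |
| 0.7 | 1.18 | 0.140 | 0.152 |

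**Baselines taken after payments began.** Suppose instead that d is itself an early effect of payment. The endline gap is then τ, so the change score gives τ − d and the lagged-outcome model τ − β1·d. With d = 0.1 and β1 = 0.5 the biases are −0.10 and −0.05 SD.

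**The case against.** A lagged-outcome model is legitimate and more precise than a change score. The cohorts are adjacent, both Welsh and from the same local authorities; they are separated by birth date, and take-up was 97%. Matching precedes the analysis. The remaining gap may therefore be small, and with no gap there is no bias. The sentence on unobserved differences is a general description of the method, and the article openly calls the survey version non-standard. A fuller analysis plan exists and may list further checks.

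Much of this stands. The bias is conditional and its size rests on assumed values. The lack of a difference-in-differences version among the article's robustness checks is not a fault in itself, although none of the checks it does list would expose the discrepancy. Two limits apply. High take-up does not address who answered the survey. Matching on the baseline outcome, if that is done, would not restore common trends: where cohorts differ persistently, it brings regression to the mean.

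A reader might infer three stronger things that the documents do not support:
- **That the survey estimate is biased.** No baseline gap is reported.
- **That late baselines show the difference in differences to be the right model.** The Discussion says only that some participants answered after the pilot had started, and a gap caused by early payment biases the change score more.
- **That the change score must be primary and costs precision only when the correlation is below 0.5.** That threshold belongs to the comparison with an unadjusted endline analysis. Against the lagged-outcome model the change score is less precise at any correlation below 1.

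The mismatch itself survives. The article says the assumptions are the same as for a standard difference in differences, and the printed equation does not use them.

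**Conclusion.** The point holds as a contradiction between the stated identifying assumption and the written primary equation; it needs no numbers to establish. Its consequence is conditional: under common trends, with a residual baseline gap d, the survey coefficient is off by (1 − β1)d. For the assumed ranges that is 0.04 to 0.12 SD, or 20% to 60% of the 0.2 SD the plan expects to detect; at d = 0 it vanishes. The documents do not settle which assumption is more credible, so they do not show the lagged-outcome model to be the wrong choice. They do show that it cannot carry the claims made for it. This should be corrected before endline data are analysed.

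**What to change.** Make the text and the equation agree, by one of two routes:
1. Write the survey model as a difference in differences, either with two rows per person and a wave-by-cohort interaction or as the change score on cohort, X and L. Keep the lagged-outcome model as a named check.
2. Keep the lagged-outcome model as primary. State that it assumes no unmeasured confounding given the baseline outcome, X and local authority. Withdraw the common-trends and unobserved time-invariant claims for surveys, and add the difference-in-differences version as a named robustness check.

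Either way, report the two estimates side by side with the baseline gap. Do not label outcomes collected only at follow-up as difference in differences: they have no baseline to difference, and the article already treats them by a separate approach.

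The cost is revised wording and one extra regression per outcome. Route 1 also gives up precision (variance ratio 1.33 at a correlation of 0.5), and at a correlation of 0.3 the detectable effect of 0.233 SD would exceed the plan's 0.2 SD under the assumptions above. Neither route repairs baselines taken after payments began; that limitation has to be reported separately.

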#### Statistical methods for economic analysis

Specification of comparators and approaches for accounting for selection biases will mirror those planned for the impact evaluation [76,77]. Value for money will initially be expressed in terms of social cost-benefit at 24 months post-intervention, converting outcomes to monetary values. Accepted guidelines outlined in the HM Treasury Green Book [78] will be followed, constructed to explore the stated objectives of economy, efficiency and effectiveness.

The analysis will be informed by a comprehensive review of the broader literature regarding interventions similar to basic income, and appraisals of that funding approach. The full analysis model will include all cost and outcomes variables, in accordance with the “intention to treat” (ITT) principle. The cost-consequences analysis will make explicit the full range of the intervention’s impacts in disaggregate form. Costs and benefits will be estimated using subjective wellbeing evidence, which aims to capture the direct impact of a policy on wellbeing and broader social impacts such as engagement in education, financial literacy, and psychological well-being. Principles of opportunity cost will underpin all calculations. Missing data from either self-report, linked data or patient surveys will be imputed where appropriate to reduce the impact of missing data on regression results. A range of sensitivity analyses will be conducted to explore the impact of uncertainty surrounding key components of the economic evaluation on economic outcomes. These will be carried out for key costs and outcomes, specifically where they are highly sensitive to certain values or input variables. Sub-group analyses will mirror those undertaken for the main analysis. Summary statistics and cluster analysis may be used to determine data characteristics. Finally, narrative techniques will be used for outcomes which cannot be monetised, or where further exploration will be important, such as financial levers and incentives, mechanisms of change and unintended consequences.

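### Little's test is credited with detecting dependence on unobserved data, and the stated predictors for imputing baselines leave out the endline outcome and do not name cohort

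*Protocol article*

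**What the plan says.** All of this is in the protocol article, under Statistical methods for analysis of impact.

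- **Diagnosis.** The plan sets out to judge whether missing data are MCAR or MAR; MNAR is not named. Little's test is described as one "which determines whether the missingness is related to the observed and unobserved data". A logistic regression of a missingness indicator on covariates is added, "which will show whether relevant covariates are predictive of missingness, pointing towards the plausibility of a MAR assumption".
- **Outcomes.** "We will not make use of imputation for outcome measures as this carries substantial risks in terms of bias".
- **Baselines.** Missing baseline values are filled by MICE, "in which available baseline or demographic data for the participant are used in regression analyses to calculate the likely values of the missing variable".
- **Where the imputed value goes.** The primary survey model regresses the endline outcome on a cohort indicator, participant characteristics, local authority fixed effects and a term that "is the lagged value of the participant’s outcome measure at baseline".
- **Robustness checks.** Null imputation in place of MICE, complete-case analysis, and logistic or probit models for binary outcomes.

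The Impact evaluation section sends further analysis detail to supplementary materials, and the administrative data text refers to a Statistical Analysis Plan. Neither is shown here.

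**The concern.** There are two separate problems.

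First, the sentence on Little's test claims something no test on observed data can deliver. The test compares observed means across missingness patterns. Rejection is evidence against MCAR. Non-rejection says nothing about whether people with worse unobserved values failed to respond. The logistic model also uses observed covariates only.

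Second, an imputation model should contain the variables of the analysis model, including its dependent variable. If a missing baseline is drawn without regard to the endline outcome, the imputed records carry no association between baseline and endline beyond what the covariates explain, so the lag slope shrinks. If cohort is also left out, imputed baselines in both cohorts are pulled to a common mean and the observed gap between cohorts shrinks too. The survey comparison is not randomised and the lag is there to remove such a gap, so part of any gap would be reported as an effect of the basic income.

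**Working it through.** **Inputs from the protocol article.** 635 recipients and a detectable effect of 0.2 SD on survey outcomes (Sample size); final baseline response of 64% in the intervention group (Survey data, Discussion). So 635 × 0.64 = 406 respondents, and 36% have no baseline survey.

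**Assumptions, because the article gives no figure.** Share of analysed records with a missing baseline, m1 in the treated cohort and m0 in the comparators; true lag slope s; baseline gap g between cohorts in SD. Using 36% treats all baseline survey non-response as imputed, which is an upper case for that source of missingness. Missingness is taken as completely at random within cohort.

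**Little's test.** Simulation with 406 people, one fully observed and one partly missing variable, 3,000 runs, nominal level 5%:

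| Mechanism | Correlation of the two variables | Rejected | Bias of estimated mean |
|---|---|---|---|
| MCAR | 0 | 5.0% | 0.00 SD |
| MNAR | 0 | 5.1% | −0.23 SD |
| MNAR | 0.2 | 24% | −0.23 SD |
| MAR | 0 or 0.2 | 100% | 0.00 SD |

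The test is silent or weak in the cases with bias. It always rejects under MAR, where the maximum-likelihood mean is unbiased.

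**Imputing baselines without outcome or cohort.** To a close approximation:

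- lag slope = s × (1 − average of m1 and m0);
- gap left in the completed baselines = (1 − m1) × g + (m1 − m0) × µ, where µ = g × (1 − m1) / [(1 − m1) + (1 − m0)] is the pooled observed mean measured from the comparator mean;
- bias in the cohort effect = s × g − (lag slope) × (gap left).

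With m1 = m0 = m this reduces to s × g × [1 − (1 − m)²].

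Example with s = 0.5, m = 0.36, g = 0.2: lag slope 0.5 × 0.64 = 0.32; bias 0.5 × 0.2 × (1 − 0.4096) = 0.059.

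| m1 / m0 | s | g = 0.1 | g = 0.2 | g = 0.3 |
|---|---|---|---|---|
| 36% / 36% | 0.6 | 0.035 | 0.071 | 0.106 |
| 36% / 36% | 0.5 | 0.030 | 0.059 | 0.089 |
| 42% / 5% | 0.6 | 0.027 | 0.054 | 0.081 |
| 36% / 9% | 0.5 | 0.021 | 0.042 | 0.063 |
| 10% / 10% | 0.5 | 0.010 | 0.019 | 0.029 |

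At g = 0 the bias is nil in every row.

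**Check by simulation.** With 406 per cohort, true effect 0.20 and s = 0.5, 600 runs of 5 imputations gave these effects at 36% missing: 0.203, 0.230, 0.264 and 0.285 for gaps of 0, 0.1, 0.2 and 0.3. The lag slope was about 0.32. At 10% missing the slope was about 0.45 and the effects were 0.202, 0.212, 0.215 and 0.227. At 36%/9% and a 0.2 gap the effect was 0.244.

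- Cohort added but not outcome: 0.241 at 36% missing and a 0.2 gap. The approximation gives bias s × g × m = 0.5 × 0.2 × 0.36 = 0.036, so naming cohort alone is not enough.
- Outcome and cohort both included: 0.195 to 0.205, slope about 0.50, in every scenario.
- Complete case: 0.194 to 0.206.

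The bias takes the sign of the gap: a treated cohort with higher baselines gives an estimate that is too high, and one with lower baselines an estimate that is too low.

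**The case against.** The case on the other side has real weight.

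- **No step depends on the test.** MICE for baselines and the refusal to impute outcomes are both unconditional. A reader might infer that a non-significant Little's test would license the analysis of observed outcomes; the text does not make that link. This stands, so the first part is a factual correction that changes no analysis.
- **The predictor list is a one-clause gloss.** It excludes nothing expressly, cohort follows from date of birth and could count as demographic, and a full list may sit in the plan not shown. This stands for cohort. The endline outcome, however, lies outside baseline or demographic data on any reading.
- **The bias is conditional and visible.** Matching of adjacent Welsh cohorts, on local authority where possible, should narrow baseline gaps, and the listed complete-case analysis was unbiased in these scenarios. Both stand. But matching cannot balance a baseline outcome that was not recorded. The Discussion itself says some intervention baselines were completed some time after the pilot started and may not reflect the true baseline, so a gap cannot be ruled out.

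Two further inferences are not supported. One is that nothing checks for informative non-response. No listed check varies an MNAR assumption, but such an analysis is commonly left to the analysis plan. The other is that the economic evaluation contradicts the impact analysis by stating "Missing data from either self-report, linked data or patient surveys will be imputed where appropriate". The qualifier at the end, and the separate economic analysis plan it will follow, leave room for a consistent rule.

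**Conclusion.** The concern holds in two limited parts.

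1. The description of Little's test is wrong as written, whatever the full plan adds. Neither planned diagnostic can separate MAR from MNAR. The consequence is one of interpretation, not of analysis.
2. The stated baseline predictors omit the endline outcome and do not name cohort. If followed as written, the lag slope is attenuated in proportion to the missing share. The cohort effect is biased only if baselines differ between cohorts. With 36 to 42% of treated baselines missing, the bias is about 0.03 to 0.04 SD at a 0.1 SD gap, 0.05 to 0.07 at 0.2 and 0.08 to 0.11 at 0.3. It falls to 0.02, 0.04 and 0.06 if only 9% of comparator baselines are missing and the slope is 0.5. With 10% missing in both cohorts it is about 0.02 at a 0.2 SD gap.

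Against the stated 0.2 SD detectable effect, 0.05 to 0.07 SD is 25 to 35%. Missing shares, slopes and gaps are all assumptions. A reader might infer that the survey estimates will be biased; the article does not establish that, because it reports neither a baseline gap nor the share of analysed records whose baseline will be imputed.

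**What to change.** - Reword the sentence on Little's test: it assesses MCAR using observed data and can only give evidence against it. State that MAR versus MNAR cannot be tested from the data, and that the logistic model shows only whether observed covariates predict missingness.
- Specify that the MICE model for missing baselines includes the endline outcome, cohort, local authority and every covariate of the analysis model. The endline outcome serves as a predictor only; missing outcomes are still not carried into the analysis, so the rule against imputing outcomes is kept.
- Report the MICE result beside the complete-case analysis already listed, and explain any material difference.

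The cost is a few sentences and a little extra code, with no new data. A sensitivity analysis for informative missing outcomes and a stated rule for the economic evaluation are optional suggestions for the full plans. Response weights are also optional, and may not be feasible: some enrolment items will reach comparators only through their survey, so those items would be unknown for comparators who do not respond.
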